#### Participants

The participants will be recruited from the Tasmanian Healthy Brain Project (THBP) [31] at the University of Tasmania (UTAS) (ethics reference H0018265), and The Healthy Brain Ageing (HBA) Program [32] at the University of Sydney (protocol number 2019/271).

The THBP is a National Health and Medical Research Council (NHMRC)-funded, prospective cohort study that evaluates cognitive ageing in older adults who reside in Tasmania, Australia. Between 2010 and 2014, 556 participants aged 50 years and older were recruited (mean age 60 years) and underwent detailed neuropsychological and cognitive assessments, medical screening, and genetic tests at baseline, with detailed (4–6 hours) annual cognitive assessments for 4 years, then biennially.

The HBA is a specialist early intervention clinic and prospective cohort study that has recruited more than 1,000 participants aged 50 years and older (mean age 66 years) who have concerns about their cognition and reside in New South Wales, Australia. All receive detailed annual clinical phenotyping, including neuropsychological and medical assessments.

Participants from THBP and HBA will be invited to take part in the TAS Test study via email invitation or in person at a scheduled study visit. Inclusion criteria: Male and female adults ≥50 years old with unimpaired cognition. Exclusion criterion: Participants with impaired cognition, defined as declining cognitive trajectories measured by CANTAB Paired Associates Learning (PAL) total errors adjusted for age and sex, and a score > 1.5 SD above the mean total errors adjusted [33]. The rationale for excluding participants with impaired cognition is that, in this study, we aim to develop a test that discriminates participants with preclinical AD (unimpaired cognition and positive p-tau181) from those with healthy ageing (unimpaired cognition and negative p-tau181). Participants may withdraw from the study at any time and for any reason without any consequence to their ongoing participation in THBP or HBA. When an individual withdraws from the study, all the information collected to that point will be kept in the database for data analysis or withdrawal analysis.

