### Statistical analysis

#### Aim 1

To develop the TAS test protocol and validate it against p-tau181, data from 350 participants with no cognitive impairment will develop the model. Data from the remaining 150 participants in this validation dataset will determine the model’s sensitivity and specificity in detecting preclinical AD. Replicates of plasma biomarkers will be assessed for outliers and then averaged. Hand-movement data will be summarised for each participant. Participants with unimpaired cognition and mean p-tau181 above a diagnostic cut off will be classified as ‘preclinical AD’. We will use multiple logistic regression to model the associations between movement features and p-tau181 positivity. Covariates may include age, sex, ApoE4 genotype, years of education, and handedness. As a secondary, more agnostic approach, we will use a deep learning approach to discover features in the video and keyboard movement data that map to p-tau181 positivity. To validate the TAS Test multivariable model, we will use cross-validation for model selection to avoid overfitting and bootstrap procedures to estimate model uncertainty. We will independently validate the model using the remaining 150 participants’ data. Receiver Operating Characteristic (ROC) curves will be plotted against the positive p-tau181 cut-off to assess the sensitivity and specificity of movement models to identify the preclinical AD stage. As TAS Test is intended as a screening test, the resulting curves will allow users to make informed choices about sensitivity and specificity that align with their research or health promotion goals.

#### Aim 2

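### As written, the Aim 1 exclusion requires both a declining PAL trajectory and a score above 1.5 SD, so people with stable impairment stay in a comparison meant to be between two unimpaired groups

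*Protocol article*

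**What the plan says.** Three places in the protocol article bear on this.

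- **Methods, Aim 1, Participants (eligibility).** The inclusion criterion is "Male and female adults ≥50 years old with unimpaired cognition". There is a single exclusion criterion, impaired cognition, which the text spells out as "declining cognitive trajectories measured by CANTAB Paired Associates Learning (PAL) total errors adjusted for age and sex, and a score > 1.5 SD" (counted in the direction of more errors). Given in full, the second condition reads "and a score > 1.5 SD above the mean total errors adjusted". Aim 1 has no other operational definition of impaired or unimpaired cognition.
- **Same section (purpose and source).** The exclusion is justified by the wish for an instrument which "discriminates participants with preclinical AD (unimpaired cognition and positive p-tau181) from those with healthy ageing (unimpaired cognition and negative p-tau181". One of the two source cohorts, the Healthy Brain Ageing (HBA) Program, is a specialist early intervention clinic with more than 1,000 participants "who have concerns about their cognition and reside in New South Wales, Australia".
- **Statistical analysis, Aim 1.** The case label follows from eligibility: "Participants with unimpaired cognition and mean p-tau181 above a diagnostic cut off will be classified as" preclinical AD.

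**The concern.** The purpose of the exclusion is to keep impairment out of both arms of the comparison. A definition that needs level and decline together does this only for people who meet both. Someone well into the impaired range but not worsening passes through, and a clinic for people with cognitive concerns is a plausible place to find such participants.

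What is at stake is the meaning of the main Aim 1 result. If part of the case group is already impaired, the sensitivity, specificity and AUC describe a mixture of preclinical and symptomatic people. If part of the control group is impaired, healthy ageing is mislabelled as well. Only 85 cases are expected, about 25 of them in the validation set, so a modest number of such people changes the make-up of the case group.

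**Working it through.** **1. The rule as a truth table** (wording from Methods, Aim 1, Participants)

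| PAL trajectory | Score > 1.5 SD | Result as written |
|---|---|---|
| declining | yes | excluded |
| stable | yes | kept |
| declining | no | kept |
| stable | no | kept |

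The second row is the problem. Such a person is not impaired under the only definition given, so the label is preclinical AD if p-tau181 is positive and healthy ageing if it is negative.

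**2. The plan's own figure.** The Sample size section expects 17% of 500 to be positive: 0.17 × 500 = 85. This reproduces and does not depend on the present point.

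**3. How many people sit in row two?** The documents do not say. As an illustration, suppose a share *s* of 500 candidates scores above 1.5 SD and a share *d* of those is declining. The number kept is 500 × *s* × (1 − *d*).
- Low end: *s* = 6.7% (normal tail, P(Z > 1.5)), *d* = 75%: 500 × 0.0668 × 0.25 ≈ 8.
- High end: *s* = 20% (assumed for a cohort with cognitive concerns), *d* = 25%: 500 × 0.20 × 0.75 = 75.

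**4. Effect on case mix and AUC.** Assumed inputs: a share *p* of the 500 is impaired, with p-tau181 positivity *q*; the others have the plan's 17%; impaired people score 1 SD worse whatever their p-tau181 status; scores are normal with equal variance.

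Impaired share of cases: a = *pq* / [*pq* + (1 − *p*) × 0.17]. 
Impaired share of controls: b = *p*(1 − *q*) / [*p*(1 − *q*) + (1 − *p*) × 0.83]. 
With δ = √2 · Φ⁻¹(true AUC), 
observed AUC = [(1 − a)(1 − b) + ab] Φ(δ/√2) + a(1 − b) Φ((δ + 1)/√2) + (1 − a)b Φ((δ − 1)/√2).

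Worked case, *p* = 10%, *q* = 50%, true AUC 0.75 (δ = 0.954):
- a = 25 / (25 + 76.5) = 24.6%; b = 25 / (25 + 373.5) = 6.3%.
- AUC = 0.722 × 0.750 + 0.231 × 0.916 + 0.047 × 0.487 = 0.776.

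| *p* | *q* | Impaired share of cases | AUC if true 0.65 | if true 0.75 | if true 0.90 |
|---|---|---|---|---|---|
| 5% | 17% | 5.0% | 0.647 | 0.745 | 0.895 |
| 5% | 25% | 7.2% | 0.653 | 0.750 | 0.898 |
| 5% | 40% | 11.0% | 0.664 | 0.759 | 0.902 |
| 5% | 50% | 13.4% | 0.670 | 0.765 | 0.905 |
| 10% | 17% | 10.0% | 0.644 | 0.741 | 0.890 |
| 10% | 25% | 14.0% | 0.656 | 0.751 | 0.895 |
| 10% | 40% | 20.7% | 0.675 | 0.766 | 0.904 |
| 10% | 50% | 24.6% | 0.686 | 0.776 | 0.909 |

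The AUC of 0.90 is the one the Sample size section plans around. For scale, the Hanley-McNeil standard error at AUC 0.75 with 25 cases and 125 controls (the validation set) is 0.059.

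**The case against.** Four counter-arguments deserve weight.

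- **The conjunction may be deliberate.** The definition carries a citation that is not at hand, and Aim 2 also combines a level with a change (30 or more errors at baseline and an increase of more than 10). Requiring decline protects the 6.7% who exceed 1.5 SD under a normal distribution from being called impaired on one score. This is a fair reason for such a rule, but it does not reconcile the rule with its stated purpose, because people with stable impairment are still kept.
- **The inclusion criterion may catch these people.** Unimpaired cognition is a separate requirement, the case label repeats it, and both cohorts have detailed neuropsychological testing. A full protocol might define it. In this article, though, the only definition is the exclusion sentence, and that sentence fixes the rule rather than leaving it open.
- **A reader might infer that accuracy will be overstated.** The documents do not support that. The direction depends on p-tau181 positivity among the impaired, which is not given. At 17% the AUC falls, at 25% it hardly moves, and at 0.90 even the least favourable inputs add under 0.01. Every shift at 0.75 is less than half the validation standard error. Sampling error does not excuse bias, but it bears on the weight of the point.
- **A reader might infer that many participants lack repeat PAL scores and escape the rule for that reason.** This is not shown. Both cohorts are tested repeatedly, and the article does not say whether PAL is in their batteries.

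Simply replacing the conjunction by its alternative is also open to objection. It would remove people who are declining with a normal score. The Background links p-tau181 in unimpaired people to later decline, so they may be the very cases sought.

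**Conclusion.** The point holds on the wording. The Aim 1 definition of impaired cognition keeps people with stable PAL performance beyond 1.5 SD and lets them be labelled preclinical AD or healthy ageing, contrary to the stated aim of comparing two unimpaired groups.

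Its size cannot be derived from the documents. Under the assumed 5-10% impaired, 40-50% positive and a 1 SD deficit, 11-25% of the case group would be impaired. The AUC would be about 0.01-0.04 too high at a true value of 0.65-0.75 and at most 0.01 too high at 0.90. At 17-25% positivity it would be roughly unchanged or too low. The firm conclusion therefore concerns who is in the two groups and what the accuracy result can be said to show. It is not a claim of known inflation. The sample size calculation is not affected. The correction is worth making because it is cheap and settles the case definition.

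**What to change.** - Make a PAL score more than 1.5 SD above the adjusted mean, at the assessment nearest the TAS Test, sufficient by itself to count as impaired cognition in Aim 1. Do not make decline alone an exclusion.
- State that unimpaired cognition, in both the inclusion criterion and the case label, means not impaired under that definition.
- Whatever rule is kept, report sensitivity, specificity and AUC with and without participants above 1.5 SD.

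**Cost.** Some clinic-cohort candidates become ineligible, including some who are only in the normal tail (6.7% under a normal distribution). They must be replaced from the more than 1,500 people in the two cohorts (556 + more than 1,000). If recruitment is already under way, the sensitivity analysis alone is enough. It uses PAL scores that the present rule already requires.

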#### Measurements

Each participant will complete TAS Test online at baseline with follow-ups 3 and 6 months later. They will also be invited to provide a blood sample at baseline for p-tau181 levels. The plasma p-tau181 levels will be measured using the ultrasensitive Single Molecule Array immunoanalyser (Simoa®, Quanterix) at the University of Tasmania. Previous research established p-tau181 > 1.81 pg/ml as sensitive and specific to preclinical AD, and highly predictive of AD risk (hazard ratio 10.9) in people with unimpaired cognition or MCI [9]. However, in recognition that the research field of blood-based biomarkers is rapidly evolving [34], and the threshold levels will depend on the assay used, we will use a cut-off value determined through an examination of the most current literature.

### TAS Test protocol and data extraction

#### Consent

The online consent form is presented to participants on the password protected secure TAS Test website. It lists relevant consent statements and participants must insert their name and date of birth at the bottom of the consent form before clicking the submit button to document their consent. Repeat consent is obtained each time TAS Test is attempted.

#### Instructions

The TAS Test online protocol presents a series of general instruction screens to ensure that the participant is correctly positioned in front of their computer in a well-lit and quiet room. The TAS Test software automatically detects whether the computer camera and microphone are functioning and asks the participant for permission to use these during the forthcoming tests. If the participant does not have a camera and/or microphone on their computer, or does not give permission for their use, they may still complete sections of the assessment protocol that do not require these.

There are five sections in the TAS Test protocol:(i)Video hand movement tests(ii)Keyboard hand movement tests(iii)Visuomotor tests(iv)Visuospatial ability(v)Oro-motor and language abilities

### Video hand movement tests

A 5-second looped demonstration video of a researcher performing the required hand movements provides instructions before each new task. This is supplemented by written instructions that automatically appear on the screen and audio instructions that will be activated if the participant presses an ‘audio’ icon. For each task, the participant is instructed to hold their hands up so they can see them fitting inside green ‘data collection’ boxes that appear on the screen. A number of hand movement tasks, based on sensitivity to preclinical AD, or AD, in previous studies [19–22, 35] are tested in a fixed (non-randomised) order [1]: whole hand opening-closing in antiphase [2] finger tapping (FT) each hand separately at comfortable speed [3]; FT each hand separately at maximal speed [4]; FT both hands in-phase at maximal speed × 3 trials [5]; FT both hands anti-phase at maximal speed [6] FT both hands in phase at maximal speed with a cognitive task (counting backwards out loud from 100 i.e. dual task).

The dual motor-cognitive task has been included so we can calculate the motor cost, defined as any degradation in performance in the motor task (e.g. finger tapping) due to the additional demands of the cognitive task. People with low cognitive capacity or AD display greater dual-task motor costs than healthy age-matched controls and dual-task cost in older people with MCI is predictive of subsequent conversion to AD [36]. Audio recordings will be made during the video recording and specialised dictation software can interpret (cognitive) performance in terms of the number of correct responses and the number of errors.

Each trial is 10 seconds except for the 20 second dual motor-cognitive task. To prevent fatigue, participants initiate the start of each trial when they are ready and may take rests between trials. Participants may also stop part way through the protocol and then return to complete tests later as all interactions with the TAS Test protocol are time-stamped.

To extract the hand motor features from video data, we will develop a neural network-based computer vision method to detect and track hand keypoints (e.g. fingertip positions) in the frames of the captured video data and a model to calculate features from each individual finger tap in video data. We will use a sliding window approach to extract movement features selected by experts for analysing their correlation to preclinical AD (p-tau181 levels). We will explore an unsupervised approach using a deep network mapping directly from video clips (or keyboard-tapping data, see next section) to probability of preclinical AD. We anticipate this will give rise to discriminative spatiotemporal features in the hidden layers that could be visualised as an aid to understanding. Thus, human/supervised and agnostic/unsupervised deep learning methods will extract discriminative movement features as input data for the multivariable model (see Statistical Analysis section).

The following data will be extracted from the hand movement videos: mean tapping frequency, total tapping count, intra individual variation, mean inter tap interval, coefficient of variance of tapping frequency, coefficient of variance of amplitude, maximum speed, decrement on speed and decrement on amplitude. For the antiphase tasks, we will also measure bimanual coordination and phase shift between hands.

### Keyboard hand movement tests

Participants will be asked to complete a series of computer keyboard-tapping tasks “as fast and as accurately as you can” based on previous protocols [19, 37]. Specifically there are 8 keyboard tests in TAS Test comprising: spacebar tapping with the dominant hand for four blocks of 10 seconds tapping with 30 seconds rest periods between each block; dominant hand index finger tapping for 30 seconds alternately on two adjacent keys; dominant hand index finger tapping for 30 seconds over a defined sequence of three adjacent keys; right hand index finger tapping for 30 seconds across the keyboard between the ‘S’ key then the ‘;’ key; and left hand index finger tapping for 30 seconds across the keyboard between the ‘S’ key then then ‘;’ key. The last two tests are adapted, with permission, from the original The BRadykinesia Akinesia INcoordination (BRAIN) Tap Test developed by Noyce et al. [37] The BRAIN test was originally designed to measure motor performance in people with Parkinson’s disease. We adapted the test by instructing participants to perform the test only once with each hand (rather than two blocks of 30 seconds tapping) and using our own custom written software for data collection. All on screen instructions (Start signal, stop signal etc) and all keyboard tapping events are time-stamped in milliseconds. The following movement data will be extracted from the keyboard tapping data: tapping frequency, rhythm, intra-individual variation across repeat tasks, accuracy and delays in initiation and inhibition of movements.

### Visuomotor tests

#### Adapted version of Cats-and-Dogs test

The Cats-and-Dogs test used in TAS Test has been adapted, with permission, from the original test designed by Weil et al. [38]. The original Cats-and-Dogs test is an online test designed to detect visuoperceptual deficits in people with Parkinson’s disease; participants are shown a series of images, with each one showing either a cat or a dog, and some images skewed at an angle. There are 6 practice images followed by a test set of 16 images. Each image is presented on the screen for 450 ms, followed by a choice screen where the participant is asked to indicate whether the image shown was a cat or a dog.

In our adapted version of the Cats-and-Dogs test, we ask the participant to hold the computer mouse cursor over a ‘Start button’ at the bottom of the screen to trigger the display of each image. This modification allows additional measurements of the reaction time (time to release the start button), movement time (time to move from start button to cat/dog choice button) and latency (time to re-set the start button after the cat/dog choice button) in addition to whether the image is correctly identified (accuracy), image subject (cat vs dog) and image distortion (degree of skew distortion).

#### Reaction time tests

TAS Test includes two Reaction Time tests that measure the participant’s processing speed: a simple reaction time test (Fig. 1a) and a five-choice reaction time test (Fig. 1b). Each test has a practice phase of two trials followed by a test phase of five trials.

**Fig. 1 Fig1:**
[figure not shown]
TAS Test Reaction Time Tests: **a**) simple choice test and **b**) five choice test

The participant begins each test by clicking and holding their cursor in the light grey circle at the bottom of the screen (Fig. 1). For the simple reaction time test, there is one white circle in the centre of the screen. The participant is instructed to click on the circle as soon as it turns yellow. The circle will turn yellow after a variable, and random latency of 2, 3 or 4 seconds. Once the participant has achieved 5 out of 6 clicks correct in a row, or completed a maximum of 18 attempts, the protocol moves onto the five-choice reaction time test. In this test, five white circles are presented in the centre of the screen in a chevron formation. The participant will begin the test by clicking and holding their cursor in the grey circle. When one of the five white circles (randomly allocated) turns yellow after a variable duration (range 2–4 seconds), the participant needs to click the yellow circle as fast as possible. For each test, the participant will have to click on the grey circle to begin the next trial.

The data extracted from each test will include: an accuracy score, which is the total number of trials in which the response is recorded as correct; an error score, which is the total number of trials in which the response is recorded as incorrect (this will be split into errors of timing and errors of location); reaction time (time to release the start button), movement time (time to move from start button to yellow circle) and latency (time to re-set the start button after each trial).

### Visual and spatial working memory

#### Benson complex figure test

The Benson Complex Figure Test assesses a participant’s visuospatial ability; it is based on the Benson Figure, that was developed by Frank Benson as a simplified version of the Rey-Osterrieth complex figure [39] (Fig. 2) and has been adapted, with permission, for online use in TAS Test.

**Fig. 2 Fig2:**
[figure not shown]
Benson Figure Test (**a**) Viewing phase to register the shape over a 1-minute duration and (**b**) delayed recall phase to identify whether a sub-section was part of the original figure

In the viewing phase, participants will be shown a complex image in its entirety and have up to 1 min to commit the complex figure to memory. Participants may click “I have memorised the figure now” before the one-minute period has ended, to move on to the next task. After completing the spatial span test (see next section) participants will be asked to recall if sub-sections, that are presented on the screen in a random order, were part of the original image or not. One at a time, 20 different subsections of the Benson Figure will be randomly shown and the participant will click “YES” if they think the sub section was part of the original image, and “NO” if they think it was not. Ten of the subsection images will be from the original image and ten of them will not. The modification for TAS Test is to present the participant with sub-sections of the original shape, rather than the original task whereby the participant draws the shape from recall.

The parameters extracted from the Benson Figure Test will include: duration of original viewing phase; time between viewing phase and recall phase; recall latency, which is the mean time it takes to respond; accuracy score which is the total number of image subsets that were correctly responded to; miss score, which is the total number of image subsets that were incorrectly responded to; recall test duration, which is the total time taken to complete the recall phase.

